### Statistical analyses

Descriptive statistics (absolute and relative frequencies for variables with nominal and measures of position (mean, median) and variability measures (standard deviation, interquartile range and range) for variables with interval or ratio scaling) will be used to compare participant characteristics between the study arms.

Feasibility objectives will be quantified. If appropriate, 95% confidence intervals will be calculated based on the Wilson Score interval for binary measures. We favoured the Wilson Score interval against Wald interval due to their good properties for small numbers of trials, compared to Wei and Hutson [40]. For the analysis of the primary outcome, we will use the complete and pseudonymized data set and follow the intention-to-treat approach which includes all patients in the group they were allocated to by randomization. This approach preserves the allocation of treatment by randomization and it will be as close as possible to the ITT ideal of including all randomized patients. As sensitivity analysis, the analysis will be repeated in the per-protocol (PP) set, excluding patients with major protocol violations. Additional sensitivity analyses will explore the effects of the treatments the patients actually received. The null-hypothesis H0 (no difference occurs in the population means with regard to pain severity at T1 between the experimental intervention and the control intervention) will be tested against H1 (there is a difference in the population means of pain severity differences between the two groups at T1 and T0). Provided that the model assumptions are fulfilled, the null hypothesis will be tested using a (robust) mixed linear regression model at a significance level of 5%. The primary outcome (pain severity at T1, difference to T0) will be analysed using mixed-effects model repeated measurements after 4, 8 and 12 weeks (=T1). The analysis will be adjusted for condition, gender and baseline (T0) pain severity. Compound symmetry will be assumed. Because of the exploratory nature of the study, the observed initial signals of efficacy and utility will be considered more important than the *p*-values. The corresponding *p*-values of these tests will be interpreted purely descriptively. We will compute effect sizes and interpret them together with the respective 95% confidence intervals. Regarding secondary endpoints, exploratory data analysis will be performed using appropriate analytical methods depending on the respective parameter. Details of the statistical analyses will be fixed in a statistical analysis plan developed by the statistics department of IZKS Mainz prior to database closure. The safety analysis includes calculation and comparison of frequencies and rates of adverse events. Furthermore, statistical methods are used to assess the quality of data and the homogeneity of intervention groups. All analyses will consider gender aspects. Prior to all analyses, we will pre-specify a statistical analysis plan.

To more closely assess the ecological validity of our design in a naturalistic setting, a second analysis will be carried out where 1/3 of matched patients are randomly sampled and statistically reallocated to the non-matching arms. This is to allow a comparison between personalized treatment and truly random assignment (rather than matched vs non-matched), which may more closely mirror the ultimate implementation of personalization methods in clinical services or during a confirmatory multi-centre RCT.

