### Overview

Musculoskeletal pain patients will be offered participation in this study until at least 342 patients have been enrolled in baseline assessment and 105 patients have been included into our randomized controlled proof-of-concept study. All 105 patients enrolled in the study will undergo detailed phenotyping before and after intervention, which, together with the response/non-response data from the RCT, will serve to improve the allocation algorithm for future studies. All patients eligible will be randomly assigned 1:1 to a personalized or non-personalized treatment arm (Fig. 1). Personalization is achieved by a targeted allocation either to a therapy focused on emotional distress, a therapy focused on dysfunctional behaviours and maladaptive learning or allocation to a minimal intervention group where adaptive responses to pain will be registered. After baseline assessments (Fig. 1, T_0_) for relevant pathomechanisms, each patient included in the trial will receive either 12 weekly sessions of cluster-matching therapy (intervention arms)—where patients are allocated personalized (i.e. according to their individual pain mechanism)—or non-cluster-matching therapy (control arms) —where they are allocated non-personalized (i.e. randomly assigned between the other two interventions). After the last session, all procedures included in the baseline assessment will be performed as a posttreatment evaluation (Fig. 1, T_1_). Furthermore, a 3-month follow-up by means of telephone interview and questionnaire package will be implemented for patients taking part in the intervention study (Fig. 1, T_2_). At T_2_, the maintenance of the effects on pain and pain-related impairments will be assessed. In order to guarantee a correct evaluation of our primary outcomes in pain change, we will include an extended psychological assessment (details on outcomes are given below).

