### Interventions

The individual interventions consist of 12 weekly face-to-face sessions (EDDT, PERT), or a minimal intervention condition in which smartphone-based diary queries are monitored daily over a period of 12 weeks (EMDI). The efficacy and safety for all three treatment modules have been demonstrated in previous studies, yet their superiority in outcomes depending on patient cluster has not been formally addressed. During the trial, patients are encouraged not to change their existing therapies over the course of the therapy. All additional treatments will be recorded regularly. In order to ensure that therapy protocols are appropriate and that therapists learn to follow these protocols in early stages of the study, a subsample of pilot participants will be invited to take part in the interventions without being part of evaluation of the personalized treatment allocation algorithm to aid the quality assurance of interventions.

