### Sample size calculation

The study will be performed in an exploratory fashion and is planned as a pilot study to describe the feasibility and safety of personalized treatments for CMSP as a primary outcome, as well as an initial estimation of signals efficacy and utility as secondary outcomes. Even though a formal power calculation is not necessary in a pilot study, we nevertheless performed a power calculation to better estimate the initial signals of efficacy and utility.

For power considerations, we use a mixed-model with repeated measurements (MMRM), a two-sided significance level of 5% and a sample size of 90 patients (→45 per study arm →90 total from a total of 105 patients at an assumed dropout rate of 15%). The MMRM takes into account also the interim measurements for each patient and allows therefore a fuller use of the data than an ANCOVA. The sample size of 105 patients allows to calculate our feasibility measures with a 95% confidence interval width from 11 to 19% (for varying proportion 0.1–0.5) based on a Wald interval for binary measures [40]. Moreover, patients with data with at least one measurement can be used for the primary analysis; therefore, we expect fewer patients not to be usable for the analysis compared to an ANCOVA. Between repeated measurements, a correlation of 0.3 is assumed. Then, the study has a power of 80% to detect a true effect size of *f* = 0.22, a power of 85% for *f* = 0.23 and 90% power for a true effect size of *f* = 0.25. Dropouts will be analysed according to the underlying reasons for dropout and distinction will be made between those dropouts that are preventable by modification of study design and those that are not preventable by study design adaptations.

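### The efficacy analysis pools three clusters in which matching shifts treatment intensity in opposite directions; cluster should enter the model and the arm difference be shown per cluster, descriptively

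*Protocol article*

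**What the plan says.** **The contrast.** Statistical analyses in the Protocol article tests equality of the two allocation arms on pain severity against the alternative that "there is a difference in the population means of pain severity differences between the two groups at T1 and T0". A mixed model uses the visits at weeks 4, 8 and 12. Its listed terms are condition, gender and pain severity at T0. The Blinding section uses *condition* for the arm (personalized or non-personalized), so it does not stand for cluster. Neither cluster nor a condition-by-cluster term is listed.

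**The allocation.** Randomization and allocation stratifies by cluster. Within each cluster half of the patients receive the matching module and a quarter receive each of the two others. The distress cluster is matched to EDDT, the dysfunctional cluster to PERT and the adaptive copers to EMDI. EDDT and PERT are 12-session therapies given in person. EMDI is a smartphone diary, and the Overview calls this option "allocation to a minimal intervention group where adaptive responses to pain will be registered".

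**The aims.** Objectives asks for an initial estimate of how the personalized approach as a whole compares with the non-personalized one. Interventions states that the three modules have each been shown to be effective and safe, "yet their superiority in outcomes depending on patient cluster has not been formally addressed". Overview and Treatment personalization say that the trial's data will be used to improve the allocation algorithm for a later multicentre trial.

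**The concern.** In two clusters, personalized allocation means more 12-session therapy than the controls receive. In the third it means none, while every control receives it. The pooled difference therefore combines two things: the effect of matching, and the effect of giving the arms different amounts of intensive therapy. The second has a different sign in different clusters, and its net weight depends on how many adaptive copers are recruited.

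At stake is what the pilot can pass on. A near-zero pooled difference could come from three weak matches, or from two useful ones offset by a third. A positive one would not show whether all three matches contributed. The later trial must decide how to allocate patients, and for that the cluster-level pattern is more informative than the average.

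**Working it through.** **1. The plan's own power figure.** Inputs from Sample size calculation: "a two-sided significance level of 5% and a sample size of 90 patients", "Between repeated measurements, a correlation of 0.3 is assumed", and "the study has a power of 80% to detect a true effect size of *f* = 0.22". Three post-baseline visits come from Statistical analyses. For a between-arm F test on repeated measurements,

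λ = f² × N × m / (1 + (m − 1) × ρ), with 1 and N − 2 degrees of freedom.

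With N = 90, m = 3 and ρ = 0.3, λ = f² × 270 / 1.6 = 168.75 × f².

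| f | λ | Power | Stated |
|---|---|---|---|
| 0.22 | 8.17 | 80.7% | 80% |
| 0.23 | 8.93 | 84.0% | 85% |
| 0.25 | 10.55 | 89.5% | 90% |

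The stated figures reproduce to within about one percentage point. They refer to one overall effect and assume nothing per cluster.

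**2. Share of patients on a 12-session therapy, from the allocation rules.**

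| Cluster | Matched | Control | Difference |
|---|---|---|---|
| Distress | 1 (EDDT) | 0.5 (half PERT, half EMDI) | +0.5 |
| Dysfunctional | 1 (PERT) | 0.5 (half EDDT, half EMDI) | +0.5 |
| Adaptive copers | 0 (EMDI) | 1 (half EDDT, half PERT) | −1.0 |

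This table needs no assumption about effects.

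**3. What enters the pooled contrast.** Let D be the difference in pain relief, in SD units, between a 12-session therapy and the diary regardless of match, and let M be the effect of matching itself in a cluster. The contrast in a cluster is M + D × (share difference). Averaged over clusters, with p3 the share of adaptive copers, the D part is

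D × [0.5 × (1 − p3) − 1.0 × p3] = D × (0.5 − 1.5 × p3).

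The document does not give p3, so it is assumed here:

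- p3 = 20%: 0.5 − 0.30 = +0.20, so +0.20D
- p3 = 33%: 0.5 − 0.50 = 0
- p3 = 50%: 0.5 − 0.75 = −0.25, so −0.25D

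The same protocol run on a different case mix would thus give a different pooled estimate, even if matching did nothing.

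**4. Different patterns, same pooled value.** Take equal thirds and purely illustrative effects. Cluster differences of 0.22, 0.22 and 0.22 average to 0.22. Differences of 0.44, 0.44 and −0.22 average to (0.44 + 0.44 − 0.22)/3 = 0.22. The pooled contrast cannot separate the two. With no matching effect and D = 0.44, the cluster contrasts are +0.22, +0.22 and −0.44, and their average is 0. So equal thirds remove the intensity term from the average but do not make the average interpretable by cluster.

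**5. Precision of cluster-specific estimates.** For the mean of three visits, SE = √[(4/N) × (1 + 2 × 0.3)/3].

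- N = 30 (equal clusters, assumed): √(0.1333 × 0.5333) = 0.267; × t(28 df) 2.05 gives ±0.55 SD
- N = 18: ±0.73 SD
- N = 45: ±0.44 SD

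With 30 patients in a cluster, power at f = 0.22 is 36%, and 80% power needs f of about 0.39 (d of about 0.78). A 2-df condition-by-cluster test has 20% power if the cluster effects are 0.44, 0.44 and 0, and 66% if they are 0.44, 0.44 and −0.44. These estimates can describe but cannot decide.

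**The case against.** **Subgroup estimates are ordinary SAP content.** The article announces a separate analysis plan, which is not at hand, and stratification makes cluster estimates obtainable. This stands in part: nothing rules such estimates out. But the article does fix the contrast and list the model terms, and the stratification factor is not among them. That is a stated choice.

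**The pooled contrast is the right one for the objective.** This stands. The objective compares one allocation strategy with another, and averaging over patients is then the natural target, including a less intensive option for one cluster. The contrast is incomplete, not invalid.

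**Opposite effects are nowhere predicted.** A reader might infer that the plan expects adaptive copers to lose from matching. The document does not support this. It describes matching as the best fit in every cluster and says that the diary may be useful and safe for this one. A reversal would need an intensity effect larger than the matching effect, and no figure is given for either. What is opposite in sign is the difference in treatment intensity.

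**The power statement is not damaged.** A reader might also infer that the stated 80% falls once a smaller effect is assumed in one cluster. It does not: the 80% is conditional on an overall f of 0.22, and it reproduces. Lower values follow only from assumed cluster effects.

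**The plan has other analyses.** It mentions sensitivity analyses by treatment received, a second analysis moving a third of matched patients to the other arm, and use of response data for the algorithm. None is described as a matched-versus-mismatched comparison within cluster.

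**Efficacy is secondary and p-values are descriptive.** This stands and limits the consequence. The feasibility verdict does not use the efficacy result.

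**Conclusion.** The point holds in a limited form. The listed model omits the stratification factor and yields one pooled difference, while the allocation rules make the matched-minus-control share on 12-session therapy +0.5, +0.5 and −1.0 across the clusters. An intensity effect D then contributes D × (0.5 − 1.5 × p3) to the pooled result, from +0.20D to −0.25D for assumed adaptive-coper shares of 20% to 50%. The share differences follow from the document alone. The size of D and the cluster shares are not given, so the contribution in pain units is unknown.

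The consequence is one of interpretation. The pooled estimate is valid for the strategy question in the population recruited, but it depends on that population's mix and leaves unanswered the cluster-dependent question that the article itself calls open. It does not follow that the pilot is underpowered as stated or that matching is expected to harm any cluster.

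**What to change.** In the efficacy model, add cluster as a fixed effect, since it is the stratification factor. From a model that also has a condition-by-cluster term, report the matched-minus-mismatched difference in pain change with its 95% confidence interval in each of the three clusters, beside the pooled difference. Take the pooled value from the model without the interaction, or weight the cluster differences by the observed shares, so that it is not read off a reference-cluster coefficient.

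State three things in advance: the cluster-specific results are descriptive estimates; they will not be used alone to select matches for the later trial; and the pooled effect will be interpreted together with the observed cluster mix, which should be tabulated by arm and module.

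The cost is analysis-plan wording, a few model parameters and one extra table. Sample size and conduct do not change. The downside is wide cluster intervals (about ±0.55 SD with equal clusters, wider in a smaller one), which invite over-reading unless labelled.

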### Randomization and allocation

For the allocation of the participants, a computer-generated list of random numbers will be used. Randomization for the pilot study will be carried out by the Interdisciplinary Center for Clinical Trials (IZKS) Mainz using permuted blocks of variable lengths. The randomization lists will be implemented in the electronic case report form system (eCRF) such that randomization can be performed electronically as new participants are added to the study. After providing informed consent and the acquisition of baseline data, participants will be randomly assigned to experimental intervention (personalized allocation) or control intervention (non-personalized allocation) via this eCRF system. Allocation will be managed by an independent study manager involved neither in sequence generation, assessments or treatment. All processes will be monitored and controlled for correctness by the IZKS Mainz. This process will be started only after the enrolled participants will have completed all baseline assessments and it is time to allocate the intervention. Randomization will be stratified by cluster, so that patients have a 50% chance of being allocated to the treatment matching their cluster, and 50% of being allocated to one of the two interventions (25% chance each) not matching their cluster.

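### The stated efficacy model leaves out cluster, the randomization stratum, and its arm contrast alone cannot be read as a benefit of matching

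*Protocol article*

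**What the plan says.** Under Randomization and allocation: "Randomization will be stratified by cluster". Each patient has a 50% chance of the matching module and "50% of being allocated to one of the two interventions (25% chance each) not matching their cluster".

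Under Statistical analyses, change in pain severity is analysed by a repeated-measures mixed model over weeks 4, 8 and 12, by intention to treat. The adjustment is listed in full: "The analysis will be adjusted for condition, gender and baseline (T0) pain severity". Neither cluster nor assigned module appears. The Blinding section uses the word condition for personalized versus non-personalized, so it most likely means the arm. The article also uses the word for a module and for pain disorders, but never for cluster.

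The same section ranks effect sizes with 95% confidence intervals above p-values, which are descriptive only. It plans sensitivity analyses by treatment actually received and leaves further detail to a statistical analysis plan. The Objectives compare a personalized with a non-personalized approach. Blinding is to be kept during the statistical analysis.

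**The concern.** Two separate matters arise from one sentence.

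**Stratum.** Stratified randomization balances the arms on cluster, so between-cluster differences in outcome add almost nothing to the true sampling error of the arm contrast. A model without cluster still counts them as residual variance. Its standard error then overstates the uncertainty, and part of the precision gained by stratifying is lost. The covariate list is explicit text, so a statistical analysis plan that follows it inherits the omission.

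**Module mix.** The modules differ in intensity. EDDT and PERT are 12 weekly face-to-face sessions, and EMDI is a minimal smartphone diary. If the clusters are unequal in size, one arm gets more EMDI than the other. An arm difference can then arise even if matching a module to a cluster does nothing. The pilot is meant to prepare a multicentre trial of personalization, so what this estimate means matters for planning that trial.

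**Working it through.** **1. The plan's own figure.** Inputs from Sample size calculation: "a two-sided significance level of 5% and a sample size of 90 patients" (45 per arm); "at an assumed dropout rate of 15" percent; "Between repeated measurements, a correlation of 0.3 is assumed"; "the study has a power of 80% to detect a true effect size of" f = 0.22, with 85% at 0.23 and 90% at 0.25. Statistical analyses gives m = 3 post-baseline visits.

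λ = N·f²·m / (1 + (m − 1)ρ), F test with 1 and 88 df:

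- f = 0.22: λ = 90 × 0.0484 × 3 / 1.6 = 8.17, power 80.7%
- f = 0.23: λ = 90 × 0.0529 × 3 / 1.6 = 8.93, power 84.0%
- f = 0.25: λ = 90 × 0.0625 × 3 / 1.6 = 10.55, power 89.5%

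The stated power reproduces, so sample size is not in question. The detectable effect is d = 2f = 0.44 SD.

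**2. Standard error without cluster.** The document gives no cluster effects, so these are assumed. The simulation used N = 90, 1:1 within cluster, cluster shares 40/40/20 (EDDT, PERT and EMDI clusters), no matching or module effect, one outcome at T1, baseline and gender as covariates, and 3,000 runs per scenario.

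| Cluster effect (SD) | Model SE | Empirical SE | Rejection rate |
|---|---|---|---|
| none | 0.212 | 0.216 | 5.1% |
| 0, −0.4, +0.4 | 0.222 | 0.212 | 3.8% |
| 0, −0.8, +0.8 | 0.246 | 0.216 | 2.5% |

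Ratios: 0.222/0.212 = 1.05 and 0.246/0.216 = 1.14. With cluster added, model SE is 0.212–0.213 against an empirical 0.212–0.216, and rejection is about 5%. In all three rows the mean estimate is within 0.004 of zero, so the contrast is unbiased.

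Hand check of the last row: the between-cluster mean is 0.4 × (−0.8) + 0.2 × 0.8 = −0.16 and the variance is 0.6 × 0.64 − 0.16² = 0.358. The model SE should then be √(2/45) × √1.358 = 0.211 × 1.166 = 0.246, as simulated.

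**3. Module mix.** Let p be the share of the cluster that a module fits. Its share is p in the personalized arm and (1 − p)/2 in the control arm. The difference is p − (1 − p)/2 = (3p − 1)/2.

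Suppose EMDI is 0.3 to 0.5 SD less effective for everyone and matching does nothing (both assumed). The arm contrast is then −(3p − 1)/2 times that deficit, with p the share of the EMDI cluster:

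| Cluster shares | EMDI, personalized vs control | Contrast (SD) |
|---|---|---|
| equal thirds | 33% vs 33% | 0 |
| 40/40/20 | 20% vs 40% | +0.06 to +0.10 |
| 45/45/10 | 10% vs 45% | +0.105 to +0.175 |
| 25/25/50 | 50% vs 25% | −0.075 to −0.125 |

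**4. What each added term does.** These are simulations with an EMDI deficit of 0.5 SD and shares 40/40/20. Without cluster the mean contrast is 0.094 to 0.101, and with cluster alone it is the same. With cluster and module it lies between −0.004 and 0.001, with a model SE of 0.218. The cost of the module term is 0.218/0.213 = 1.02 to 0.218/0.212 = 1.03. At 25/25/50 it is 0.224/0.213 = 1.05.

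**5. The planned reallocation analysis.** Statistical analyses also plans to move one third of matched patients, sampled at random, to the non-matching arms. A module's share in the enlarged control group becomes [(1 − p)/4 + p/6] / (2/3) = (3 − p)/8. The difference is p − (3 − p)/8 = 3(3p − 1)/8, which is three quarters of (3p − 1)/2. Most of the imbalance in mix stays.

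**The case against.** The strongest objection concerns the module mix. The stated question is whether personalized allocation beats non-personalized allocation, by intention to treat, and the article says openly that the arms differ only in how modules are assigned. Sending adaptive copers to a low-level diary is part of that policy. This stands. A reader might infer that the arm contrast is biased or spurious, but for the stated question it is neither. A module-adjusted model answers a different question and should not replace the main contrast. It also assumes one matching effect common to all clusters.

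A reader might also infer that the planned model has an invalid standard error. The document does not support that. The error arises only if cluster is prognostic beyond covariates already in the model. These carry part of the cluster information: pain severity is an MPI subscale, and gender helps to predict cluster. Where the error arises, it is conservative. On the other side, the clusters are described as differing in distress, fear of pain and comorbidity, and the Introduction links clustering to divergent treatment response, so some prognostic value is plausible.

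The consequence is limited. Feasibility and safety are primary, p-values are descriptive, and sensitivity analyses by treatment received are planned. But the weight the protocol puts on effect sizes and intervals is what makes their width and meaning matter. The treatment-received analyses, as described, do not adjust the arm contrast for cluster and module.

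**Conclusion.** The concern holds in two limited parts.

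First, the efficacy model as stated omits the factor by which the trial randomizes. The cost is precision: a standard error 0 to about 14% too large and type I error of about 2.5% to 5%, under assumed cluster effects from none to ±0.8 SD. The figures come from a single-time-point simulation. The direction carries over to the repeated-measures model, but the exact size may not.

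Second, the arm contrast is an allocation-policy effect and cannot alone be taken as evidence that matching works. Under the assumed cluster shares and EMDI deficits, the module mix contributes −0.125 to +0.175 SD, against a detectable 0.44 SD. It contributes nothing if the clusters are equal thirds. The document gives neither cluster shares nor module differences, so only the algebra is certain. At 40/40/20 even the 0.10 SD figure is under half of one standard error (0.10/0.213 = 0.47).

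**What to change.** - **Primary efficacy model:** add cluster as a three-level factor to condition, gender and baseline pain severity. This costs 2 df and no new data. Cluster alone does not reveal the arm, so it fits with a blinded analysis.
- **Main contrast:** keep personalized versus non-personalized, and describe it as the effect of the allocation policy. Report the module mix by arm beside it.
- **Supplementary model:** name in advance condition + cluster + assigned module + gender + baseline pain severity, and describe its condition term as matching net of module. State the assumption of a common matching effect across clusters. It costs 2 more df and a standard error about 2–3% larger at 40/40/20 (about 5% at 25/25/50).
- **Blinding:** cluster and module together identify the arm, and coded module labels may not hide it, because the 50/25/25 split shows which module is the match. Fix the code for both models before these labels are released to the analyst.

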### Blinding

Patients, therapists and the researchers carrying out participant assessments will be blinded to the respective condition (personalized vs. non-personalized), and success of blinding will be evaluated to explore possible source of bias. The double-blinding of patients and data collectors (i.e. patients, therapists and psychologists) is kept during the course of the study and statistical analysis will be also done with blinding maintained to avoid bias. Randomization authorities from the Interdisciplinary Center for Clinical Trials (IZKS) Mainz will be instructed to report any suspected breach of the blinding procedures.

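### The efficacy hypothesis is set at week 12, but the model described, and the power quoted for it, concern the average difference over weeks 4, 8 and 12

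*Protocol article*

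**What the plan says.** All model statements are in the protocol article, section Statistical analyses.

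- **Target.** The null hypothesis is that "no difference occurs in the population means with regard to pain severity at T1 between the experimental intervention and the control intervention". The outcome is pain severity at T1 as a difference from T0.
- **Data.** This outcome "will be analysed using mixed-effects model repeated measurements after 4, 8 and 12 weeks (=T1"), so three post-baseline measurements enter.
- **Terms and covariance.** "The analysis will be adjusted for condition, gender and baseline (T0) pain severity", followed by "Compound symmetry will be assumed". Condition means study arm, as the Blinding section uses it: "respective condition (personalized vs. non-personalized").
- **Power (Sample size calculation).** It uses an MMRM, "a two-sided significance level of 5" per cent, a "sample size of 90 patients" (45 per arm, from 105 "at an assumed dropout rate of 15" per cent) and a correlation of 0.3 between measurements. The result is 80%, 85% and 90% power for f = 0.22, 0.23 and 0.25.
- **Time course.** None is assumed. The end of the Outcomes section uses the T0-to-T1 change for endpoints 1–6 and says the endpoints will also be looked at after 4 and 8 weeks, to study how therapy effects develop.
- **Use of the result.** Effect sizes with 95% confidence intervals take precedence over p-values, which are descriptive. Further detail is left to a statistical analysis plan.

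**The concern.** A model with one condition coefficient for three visits forces the arm difference to be the same at each visit. If the true difference changes over the 12 weeks of therapy, the coefficient is not the week-12 difference that the hypothesis names. The Outcomes section plans to study that change, so a flat course is not taken for granted.

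The effect size and its interval are what the trial intends to interpret, and the pilot is meant to prepare a multi-centre trial. An average carried forward under the label T1 would misdescribe what was estimated. If the analysis instead reports a true week-12 contrast, the published power no longer belongs to it.

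**Working it through.** **1. Reproducing the stated power.** Inputs from Sample size calculation: N = 90, two arms, two-sided 5%, ρ = 0.3. The number of measurements m is not given there; m = 3 is taken from Statistical analyses. For the between-arm effect averaged over m visits, λ = N·f²·m / (1 + (m−1)ρ), with an F test on 1 and 88 df.

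- f = 0.22: λ = 90 × 0.0484 × 3 / 1.6 = 8.17, power 80.7%
- f = 0.23: λ = 90 × 0.0529 × 3 / 1.6 = 8.93, power 84.0%
- f = 0.25: λ = 90 × 0.0625 × 3 / 1.6 = 10.55, power 89.5%

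Solving for f at exactly 80, 85 and 90% gives 0.218, 0.233 and 0.252, which round to the stated values.

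**2. Other readings with N = 90 and ρ = 0.3.**

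| Target | f = 0.22 | f = 0.23 | f = 0.25 |
|---|---|---|---|
| Stated | 80% | 85% | 90% |
| Average of 3 visits | 80.7% | 84.0% | 89.5% |
| One visit (week 12), unadjusted | 54% | 58% | 65% |
| Average of 2 visits | 73% | 76% | 83% |
| Average of 4 visits | 85% | 88% | 93% |
| Arm-by-time interaction, 3 visits | 98% | 99% | 99.5% |

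Of these, only the three-visit average fits. Adjusting the week-12 comparison for baseline at ρ = 0.3 divides λ by 1 − 0.3² = 0.91: 4.36 / 0.91 = 4.79, or 58% at f = 0.22.

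**3. What the described model estimates.** Under compound symmetry with complete data, the generalised least-squares estimate of a condition term without interaction is (δ4 + δ8 + δ12) / 3. As a share of δ12, under assumed courses:

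| Course (weeks 4, 8, 12) | Mean / T1 effect | Understatement |
|---|---|---|
| 1, 1, 1 | 1.00 | 0% |
| 2/3, 1, 1 | 0.89 | 11% |
| 1/3, 2/3, 1 (linear) | 0.67 | 33% |
| 0, 1/2, 1 | 0.50 | 50% |
| 0, 0, 1 | 0.33 | 67% |

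**4. Simulation check.** Setting: 45 per arm, ρ = 0.3, true T1 difference 0.50 SD, linear build-up, 150 replicates.

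| Model | Complete data | 15% dropout |
|---|---|---|
| Terms as described | 0.354 | 0.335 |
| Visit main effect added | 0.354 | 0.335 |
| Condition-by-visit, read at week 12 | 0.515 | 0.511 |

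The missing interaction therefore causes the averaging; adding a visit main effect alone changes nothing. With a constant effect and complete data, the first and third models agree (0.488 and 0.493).

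**5. Precision, and coverage of the T1 value.** Adjusted for baseline, in SD units at N = 90:

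- average: residual variance 1.6/3 − 0.09 = 0.443, SE = √(4/90 × 0.443) = 0.140
- week 12: residual variance 0.91, SE = √(4/90 × 0.91) = 0.201

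Take a true T1 effect d = 2f = 0.44. Under linear build-up the estimate centres on 0.44 × 2/3 = 0.293, a bias of 0.147 or 1.04 SE. The nominal 95% interval then covers the T1 value about 82% of the time. Under (0, 1/2, 1) it centres on 0.22 and coverage is about 65%.

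**The case against.** The strongest reply is that the quoted sentence lists adjustment variables in a condensed article. It does not say that no other fixed term exists, the model is called an MMRM, and details are deferred to a plan that is not shown. A reader might infer that visit terms have been ruled out for the final analysis. The documents do not support that; the unseen plan may contain them.

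The reply does not remove the point. The list includes condition itself, so it reads as more than nuisance covariates. The power statement independently fits the visit average. If the plan adds a week-12 contrast, the published power is for a different quantity. Target, described model and power disagree within the article.

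Other replies stand in full:

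- The interval is valid for the average. It is too narrow only when presented as an interval for T1.
- The average is a defensible target. Under linear build-up at d = 0.44 its root mean squared error as an estimate of T1, √(0.147² + 0.140²) = 0.203, is about that of the week-12 contrast, 0.201. With an earlier plateau it does better.
- Feasibility and safety are primary, no feasibility criterion uses this coefficient, and p-values are descriptive. With no effect at any visit, the model remains valid.

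**Conclusion.** The point holds as a mismatch inside the article: hypothesis and outcome at week 12, a described model that yields the 12-week average, and power that reproduces for that average. The step-1 match rests on three measurements, a number inferred from the analysis section.

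The size of any bias is conditional. It is zero for an effect constant from week 4, and about 11%, 33%, 50% or 67% of the T1 effect under the build-up courses above. A reader might settle on one third as the bias. That figure belongs to linear build-up from zero with complete data, and the article assumes no course. A reader might also infer that the later trial would be 2.25 times too large, that is (3/2)². This needs the same linear assumption and a trial sized on this estimate alone; the article says only that the pilot prepares that trial.

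Severity is moderate, because efficacy is a secondary, exploratory objective.

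**What to change.** Choose one target and make hypothesis, model and power agree.

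- **Keep T1.** Add visit and condition-by-visit to the fixed terms, and report the week-12 condition contrast with its 95% CI as the T1 effect. Report the 12-week average as well, under that name. Restate the power for the week-12 contrast: at f = 0.22, about 54% without and 58% with baseline adjustment, at correlation 0.3.
- **Or declare the average.** Name the mean difference over weeks 4, 8 and 12 as the target and reword H0 and H1. The stated power then stands, but the result must not be called the T1 effect.

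Neither option needs extra data or patients. The cost of the first is a larger standard error (about 0.20 versus 0.14 SD) and a less favourable stated power. The cost of the second is giving up the week-12 claim.
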